## Abstract

**Background:**

Atrial fibrillation (AF) is one of the commonest arrhythmias observed in general practice. The thromboembolic complications of AF include transient ischemic attack, stroke, and pulmonary embolism. Early recognition of AF can lead to early intervention with managing the risks of these complications.

**Objective:**

The primary aim of this study is to investigate if patients are managed in general practice according to current national guidelines. In addition, the study will evaluate the impact of direct oral anticoagulant use with respect to AF complications in a real-world dataset. The secondary aims of the study are to develop a dashboard that will allow monitoring the management of AF in general practice and evaluate the usability of the dashboard.

**Methods:**

The study was conducted in 2 phases. The initial phase was a quantitative analysis of routinely collected primary care data from the Oxford Royal College of General Practitioners Research and Surveillance Center (RCGP RSC) sentinel network database. AF cases from 2009 to 2019 were identified. The study investigated the impact of the use of anticoagulants on complications of AF over this time period. We used this dataset to examine how AF was managed in primary care during the last decade. The second phase involved development of an online dashboard for monitoring management of AF in general practice. We conducted a usability evaluation for the dashboard to identify usability issues and performed enhancements to improve usability.

**Results:**

We received funding for both phases in January 2019 and received approval from the RCGP RSC research committee in March 2019. We completed data extraction for phase 1 in May 2019 and completed analysis in December 2019. We completed building the AF dashboard in May 2019. We started recruiting participants for phase 1 in May 2019 and concluded data collection in July 2019. We completed data analysis for phase 2 in October 2019. The results are expected to be published in the second half of 2020. As of October 2020, the publications reporting the results are under review.

**Conclusions:**

Results of this study will provide an insight into the current trends in management of AF using real-world data from the Oxford RCGP RSC database. We anticipate that the outcomes of this study will be used to guide the development and implementation of an audit-based intervention tool to assist practitioners in identifying and managing AF in primary care.

**International Registered Report Identifier (IRRID):**

RR1-10.2196/21259

## Introduction

Atrial fibrillation (AF) is one of the commonest arrhythmias observed in clinical practice [1]. Globally, the incidence of AF is rising. The thromboembolic complications of AF can lead to significant disabling consequences for patients, including transient ischemic attack, stroke, and pulmonary embolism. Early recognition of AF in general practice can lead to early intervention with managing the risks of these complications.

Current guidelines on the management of AF by the National Institute for Health and Care Excellence (NICE) advise identifying and managing the underlying causes of AF, treating the arrhythmia, and assessing and managing the risk of stroke in these patients [2]. Risk of stroke is determined by the CHA_2_DS_2_-VASc (Congestive heart failure, Hypertension, Age, Diabetes, previous Stroke/transient ischemic attack–VAScular disease) assessment tool [3], which guides the practitioner on commencing anticoagulation treatment to manage this risk. The risk of starting a patient on anticoagulation is assessed using the HAS-BLED (Hypertension, Abnormal renal/liver function, Stroke, Bleeding history or predisposition, Labile international normalized ratio, Elderly, Drugs/alcohol concomitantly) score, assessing for major bleeding risks [4].

Anticoagulation therapy aims to reduce the risk of thromboembolic events. This has been achieved using warfarin (a vitamin K antagonist) for many years. The introduction of direct oral anticoagulants (DOACs) such as apixaban and rivaroxaban to clinical practice has changed how AF is managed in clinical practice [5]. In comparison to warfarin, DOACs are observed to have similar or better mortality and vascular outcomes [6]. They have the added benefit of requiring no monitoring, as opposed to warfarin use [7]. Though studies have highlighted that increased number of patients in clinical practice are receiving treatment for AF [8], whether they are managed according to national or local guidelines is unclear. Better understanding of current management trends of AF in population will guide practitioners on how best to employ interventions in clinical practice to increase awareness of AF and early recognition.

The aim of this study is to understand the disease and prescribing trends related to AF in general practice. We also aim to develop a system to monitor practice-level indicators for AF of the same trends and evaluate the usability of this system. The primary objective of this study is to investigate if people with newly diagnosed AF treated with DOACs versus warfarin have any difference in stroke or all-cause mortality in long-term follow-up. The secondary objectives of this study are to develop an AF dashboard as an intervention method at a practice level and to evaluate the usability of the AF dashboard.

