## Methods

### Study Design

This study combines qualitative and quantitative methods and therefore, was planned as a mixed method study [9-11]. It was run within the Oxford Royal College of General Practitioners Research and Surveillance Centre (RCGP RSC) sentinel network of general practices. The mixed method study was conducted in 2 phases. Phase 1 was a quantitative analysis of AF data. We conducted a repeated cross-sectional study to identify those patients diagnosed with AF during 2009-2019 and identified current therapeutic management of their AF. Phase 2 involved development and evaluation of a dashboard for monitoring data quality for AF. The dashboard provides the general practices in the RCGP RSC sentinel network an access to quality indicators related to AF management that are updated weekly.

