#### Exposures and Outcomes

We considered the exposure as continuous anticoagulant prescription for the first time after receiving an AF diagnosis. Although almost all anticoagulant prescriptions in the United Kingdom are issued from primary care if an anticoagulant is started in a hospital, we measured exposure from the first general practice prescription. We excluded patients who had an interval of greater than 90 days between anticoagulant prescriptions.

Outcomes are first records of stroke and all-cause mortality based on previously published Read codes [16,17] Stroke was included regardless of etiology, an approach used in other studies [18,19]. Study participants were followed for stroke and all-cause mortality till the end of the study period.

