### Statistical Analysis

Analysis of data extracted from general practice CMR was carried out using the statistical software R. We studied the influence of the anticoagulation regimen by evaluating the cause-specific hazard ratio and the subdistribution hazard ratios of both events. Additionally, we estimated cumulative incidence for both events by direct regression, utilizing the inverse of the probability of censoring weights method [15] with time-varying effects [20]. We will report and interpret both cause-specific and subdistribution analyses. The cause-specific hazard ratio is often interpreted as estimating etiological association, estimating associations between covariates, and the rate at which events occur in those participants who are event-free. The cause‐specific hazard ratio can be interpreted as a rate ratio. Whenever the proportional hazards assumption was violated, we interpreted all hazard ratios as time-averaged effects.

We will determine the (adjusted) incidence and prevalence of AF for each year along with the proportion of incident and prevalent cases treated with nothing, antiplatelet medications only (eg, aspirin), and anticoagulant therapy (warfarin/types of DOACs). We will also determine the number of strokes, transient ischemic attacks, deaths, and bleeds in the incident and prevalent cases per year.

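### The primary objective concerns newly diagnosed AF, but a first anticoagulant at any time after diagnosis counts and time since diagnosis is not adjusted for, so AF duration can confound DOAC versus warfarin

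*Protocol article*

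**What the plan says.** In the Introduction, the primary objective is to "investigate if people with newly diagnosed AF treated with DOACs versus warfarin have any difference in stroke or all-cause mortality in long-term follow-up". Study Design says the study will "identify those patients diagnosed with AF during 2009-2019". Case Ascertainment asks for an adult with an AF code and some registration within 2008 to 2019, and excludes previous stroke without saying at which date this is judged.

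Exposures and Outcomes defines exposure as "continuous anticoagulant prescription for the first time after receiving an AF diagnosis" and adds that "we measured exposure from the first general practice prescription". The only interval rule in that section is "We excluded patients who had an interval of greater than 90 days between anticoagulant prescriptions", which governs gaps between successive prescriptions and not the gap from diagnosis to the first one.

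Covariates lists age band, gender, deprivation quintile, comorbidities from the stroke risk score (stroke or transient ischaemic attack among them) and smoking. Time since AF diagnosis and calendar period of starting treatment are not listed. Statistical Analysis plans to describe each year the "proportion of incident and prevalent cases treated with nothing, antiplatelet medications only (eg, aspirin), and anticoagulant therapy", so the plan expects some patients with AF to be without an anticoagulant.

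**The concern.** Under the stated rule, a patient diagnosed in 2009 who first receives an anticoagulant in 2017 enters on the same footing as one treated within days of diagnosis. The first had long-standing AF at treatment start and is not newly diagnosed in the sense a reader of the objective would expect.

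This matters for the comparison if the two arms contain different shares of such patients. The Introduction says that warfarin had been in use for many years before DOACs were introduced. Someone left untreated early in the period could have a DOAC as an option only after a wait. Late starters also differ from early starters in a way tied to the outcomes: they had to stay alive until the first prescription. If previous stroke is judged at that date, they also had to stay free of stroke. Such survivors may have a lower event rate. Against that, patients earlier thought unsuitable for anticoagulation may have a higher one. The estimate could be shifted either way, and no listed covariate measures AF duration.

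**Working it through.** The plan states no figure on this point, so there is none to reproduce. The check has three parts.

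**1. Longest wait the text allows.** Diagnoses start in 2009 (Study Design) and extraction was complete in May 2019 (Results): 2019 + 5/12 − 2009 = 10.42 years. It could be longer if the registration rule in Case Ascertainment lets in diagnoses before 2009.

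**2. Mixing late and early starters.** All inputs are assumed. Let pD and pW be the shares of late starters among DOAC and warfarin patients, r the event rate of late relative to early starters, and the true hazard ratio 1. Then

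observed ratio = (1 − pD + pD·r) / (1 − pW + pW·r).

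| pD, pW | r = 0.7 | r = 1.3 | r = 1.5 |
|---|---|---|---|
| 0.30, 0.10 | 0.91/0.97 = 0.94 | 1.09/1.03 = 1.06 | 1.15/1.05 = 1.10 |
| 0.40, 0.10 | 0.88/0.97 = 0.91 | 1.12/1.03 = 1.09 | 1.20/1.05 = 1.14 |

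**3. Survivor selection alone.** This asks how far r could fall merely because late starters stayed event-free. Under a gamma frailty with variance θ and mean hazard h per year, those still event-free after t years have 1/(1 + θht) times the initial mean hazard. The assumed ranges are h = 0.05 to 0.10 and θ = 0.25 to 1.0.

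- t = 3: from 1/1.0375 = 0.96 to 1/1.30 = 0.77
- t = 5: from 1/1.0625 = 0.94 to 1/1.50 = 0.67

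A simulation then put this into the design:

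- 1,000,000 patients per run, diagnosed evenly from 2009 to mid-2019, with no drug effect and h = 0.10.
- DOACs arrive in 2011 or 2013 (the documents give no date).
- A share q of those diagnosed before arrival waits, and starts a DOAC within 3 years of arrival.
- All others start within 3 months of diagnosis: warfarin before DOAC arrival, half and half after it.
- Follow-up is at most 2 years from first prescription. Any event during the wait removes the patient.

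| Arrival | q | θ | DOAC starters more than 1 year after diagnosis | Rate ratio, no limit | Rate ratio, 3-month limit |
|---|---|---|---|---|---|
| 2011 | 0.2 | 0.5 | 6% | 0.993 | 0.998 |
| 2011 | 0.2 | 1.0 | 7% | 0.988 | 1.003 |
| 2011 | 0.4 | 0.5 | 12% | 0.993 | 1.000 |
| 2011 | 0.4 | 1.0 | 12% | 0.968 | 1.014 |
| 2013 | 0.2 | 0.5 | 15% | 0.984 | 0.992 |
| 2013 | 0.2 | 1.0 | 15% | 0.965 | 0.999 |
| 2013 | 0.4 | 0.5 | 26% | 0.965 | 1.001 |
| 2013 | 0.4 | 1.0 | 26% | 0.930 | 1.016 |

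The last column shows how far this crude ratio strays from 1 without late starters, so differences of about 1% between columns mean little. With no limit the ratio is 0.93 to 0.99; with one it is 0.99 to 1.02. The simulation sends all waiters to DOAC and models only survivor selection, so it cannot produce a shift above 1 from sicker late starters. Neither calculation applies the planned covariate adjustment.

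**The case against.** The strongest reply is that newly diagnosed can mean incident within the study period. The exposure rule is then an ordinary new-user rule in incident AF, and any limit on the wait belongs in a full protocol that is not shown. This stands in part: the absence of a stated limit is not by itself an error. It does not dispose of the point. The article states its exposure rule and its covariates, and followed as written they put new and long-standing AF into one model with nothing for AF duration.

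Survival to treatment start is also common to every new-user cohort, and late warfarin starters are admitted too. If follow-up starts at first prescription, as the exposure wording suggests, no immortal time arises. That is fair. What remains is confounding by AF duration if the shares differ between arms. The start of follow-up is not stated outright, and if it were the diagnosis date the untreated wait would be immortal time.

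Adjustment for age band, comorbidities and smoking would probably absorb part of any difference, so the figures above may overstate what is left.

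A reader might infer two stronger things. One is that late DOAC starters are necessarily selected to be stroke-free. That requires previous stroke to be judged at first prescription, but no reference date is given, and stroke also appears as a baseline covariate. The other is that patients passed over for warfarin built up and entered mainly as DOAC starters. This is plausible, but no section documents it. The yearly treatment proportions in Statistical Analysis are descriptive and say nothing about who later started what.

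**Conclusion.** The concern holds as one of possible confounding. The objective concerns newly diagnosed AF, the exposure rule sets no bound on the wait, and AF duration is outside the listed covariates. Because DOACs were introduced later than warfarin, an imbalance in AF duration between the arms is credible.

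Size and direction cannot be derived from the documents, which give no distribution of waiting times and no date of DOAC introduction. The range of 0.91 to 1.14 rests on assumed shares of 30% or 40% against 10%, higher than the 6% to 26% of DOAC starters beginning more than a year late in the simulation. The simulated 0.93 to 0.99 covers one mechanism only. A reader might take these figures as an estimated bias, or as showing that DOACs would be favoured; they support neither. They show that a shift of several per cent is possible under no drug effect, which is enough to justify a cheap adjustment. Adjusting for calendar year of start would not replace it, because new and long-standing cases start in the same year.

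**What to change.** Add time from first AF code to first anticoagulant prescription as a covariate in the DOAC-versus-warfarin models, both cause-specific and subdistribution. Report the same comparison restricted to patients who start within a fixed window of diagnosis, for example 90 days, with later starters shown separately. Tabulate the waiting time by arm so that readers can see whether an imbalance exists. State the date at which previous stroke is judged and reconcile that exclusion with stroke as a baseline covariate.

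The window length is a choice of target population, which is why the restriction is proposed as a reported analysis alongside the adjusted one and not as the only cohort. The cost is one added covariate, fewer patients in the restricted analysis, and a rerun. Both dates should be available in the extracted data, since the exposure definition needs them. The article reports analysis complete in December 2019 and publications under review in October 2020, so the rerun would have to be fitted into that process.

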## Methods

### Study Design

This study combines qualitative and quantitative methods and therefore, was planned as a mixed method study [9-11]. It was run within the Oxford Royal College of General Practitioners Research and Surveillance Centre (RCGP RSC) sentinel network of general practices. The mixed method study was conducted in 2 phases. Phase 1 was a quantitative analysis of AF data. We conducted a repeated cross-sectional study to identify those patients diagnosed with AF during 2009-2019 and identified current therapeutic management of their AF. Phase 2 involved development and evaluation of a dashboard for monitoring data quality for AF. The dashboard provides the general practices in the RCGP RSC sentinel network an access to quality indicators related to AF management that are updated weekly.

### Phase 1: Quantitative Analysis of AF Data

#### Data Source

The initial phase involved a repeated cross-sectional retrospective analysis of data extracted from the RCGP RSC database, a surveillance network, which collects data from computerized medical records (CMR) from more than 3.5 million patients and over 300 general practices in England. CMRs are used during consultations to record patient conditions and prescriptions [12,13]. Anonymized clinical coded data from participating general practices were uploaded weekly to a secure network at the Clinical Informatics Research Group [12,14]. This study used NICE guidelines as the standard to compare the management of AF across this database.

#### Case Ascertainment

We used Read codes and CTV3 codes used in primary care CMR systems to identify patients with AF. Pay-for-performance (P4P) for chronic disease management has improved data quality related to AF in the recent past [15]. We excluded patients who had a previous stroke and those not on British National Formulary–recommended dose of DOAC. We included patients over 18 years with code for the diagnosis of AF who had been registered at any point between 2008 and 2019.

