## Discussion

The RCGP RSC sentinel network has a large dataset, which is representative of information regarding primary care practices on management of AF. The quantitative analysis will report on the current trends of anticoagulant prescribing using a real-world data set in the United Kingdom and the overall population effect of the use of DOAC use.

Missing/incomplete data could be a potential issue in this analysis. We intend to reduce the effect of this issue by incorporating an ontological approach, considering practice level variations in the anticoagulation prescribing.

The qualitative analysis of the dashboard will indicate the priority of sections that require an improved user experience. We intend to enhance the dashboard using the outcomes of the usability study and deploy to general practices in the RCGP RSC sentinel network.

As the incidence of AF has increased over the years, there is a greater focus on early recognition of AF in general practice to allow for early intervention. This study will give insights into the current trends in management of AF using real-world data from the Oxford RCGP RSC database. We anticipate that the outcomes of this study will be used to guide the development and implementation of an audit-based intervention tool for use in primary care settings to assist practitioners in identifying and managing AF.

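### The Abstract and Introduction name different primary questions, and exclusions set for all of Phase 1 restrict the population for the guideline and trend analyses

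*Protocol article*

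**What the plan says.** **Primary question.** The Abstract (Objective) says: "The primary aim of this study is to investigate if patients are managed in general practice according to current national guidelines". It adds the drug question second: "In addition, the study will evaluate the impact of direct oral anticoagulant use with respect to AF complications in a real-world dataset". The Introduction opens its statement of purpose with "The aim of this study is to understand the disease and prescribing trends related to AF in general practice" and then says: "The primary objective of this study is to investigate if people with newly diagnosed AF treated with DOACs versus warfarin have any difference in stroke"; death from any cause is named there as the other outcome. Guideline concordance is not listed there as a primary or secondary objective. It returns in Methods, Data Source: "This study used NICE guidelines as the standard to compare the management of AF across this database".

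**Population.** Case Ascertainment, under Phase 1, says: "We excluded patients who had a previous stroke and those not on British National Formulary–recommended dose of DOAC". It then includes adults with a coded AF diagnosis. Exposures and Outcomes adds a further exclusion for gaps longer than 90 days between anticoagulant prescriptions. Neither section limits its exclusions to a particular analysis.

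**Analyses.** Statistical Analysis plans the hazard models for the anticoagulation regimen. It also plans yearly AF incidence and prevalence, the shares of cases that are untreated, on antiplatelets only or anticoagulated, and yearly counts of strokes, transient ischemic attacks (TIA), deaths and bleeds. Covariates lists baseline stroke or TIA among the adjustment variables. The Discussion expects to report "the overall population effect of the use of DOAC use".

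**The concern.** The two candidate primary questions need different populations. Whether care follows guidelines is a question about all AF patients, including those untreated, undertreated or dosed outside the formulary. DOAC versus warfarin is a question about new anticoagulant users, where excluding earlier stroke makes sense because the outcome is a first stroke record. One set of exclusions, placed at case ascertainment, appears to serve both.

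Two things are at stake. A reader cannot tell which result is primary. And if the exclusions govern the descriptive work, part of the guideline question is settled by the selection, and the yearly figures leave out a group defined by a component of the stroke-risk score that the Introduction says guides anticoagulation.

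**Working it through.** Phase 1 states no sample size, rate or effect size, so there is no figure of the plan to reproduce. The check sets the sections side by side and works out what the exclusions imply.

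**1. Primary question.** Abstract: guideline management is primary and DOAC impact is additional. Introduction: DOAC versus warfarin is primary and guideline management is not named as an objective. The two statements conflict.

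**2. Reach of the exclusions.** Read literally, the dose clause would remove everyone not taking a recommended DOAC dose, including warfarin and untreated patients. That would defeat both the drug comparison and the planned treatment shares, so the sensible reading is that it removes DOAC users on a non-recommended dose. On that reading, untreated and antiplatelet-only patients stay in.

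**3. Dose concordance.** Retained DOAC users on a recommended dose / all retained DOAC users = 100%, whatever the true share.

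**4. Treated share.** Among AF patients without previous stroke, let t be the share anticoagulated and x the share of all such patients on off-dose DOAC. Off-dose users leave both numerator and denominator:

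- observed share = (t - x)/(1 - x)
- shortfall = t - (t - x)/(1 - x) = x(1 - t)/(1 - x), which is positive whenever x > 0 and t < 1.

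The documents give neither t nor x. Illustrations with assumed values, all at t = 0.70:

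| Assumption | x | Observed share | Shortfall (points) |
|---|---|---|---|
| Direct assumption | 0.08 | 0.62/0.92 = 67.4% | 2.6 |
| All anticoagulated on DOAC, 10% off-dose | 0.70 × 0.10 = 0.07 | 0.63/0.93 = 67.7% | 2.3 |
| All anticoagulated on DOAC, 25% off-dose | 0.70 × 0.25 = 0.175 | 0.525/0.825 = 63.6% | 6.4 |

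The last two rows are upper limits for their off-dose fractions, because some anticoagulated patients take warfarin.

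**5. Prevalence.** If a share s of AF patients has a previous stroke, excluding them multiplies counted prevalence by (1 - s). For an assumed s of 10% to 20%, prevalence is understated by 10% to 20%, before any loss of off-dose users. This applies only if the exclusions govern the prevalence analysis.

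**6. Drug comparison.** The previous-stroke and 90-day-gap exclusions apply to both groups; only the dose criterion is specific to DOAC. Let p be the off-dose share of DOAC follow-up and k the event-rate ratio of off-dose to on-dose users. The full-group rate relative to the on-dose rate is 1 + p(k - 1), so dropping off-dose users changes the group rate by 1/[1 + p(k - 1)] - 1.

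- k = 1.5: p = 0.10 gives 1/1.05 - 1 = -4.8%; p = 0.25 gives 1/1.125 - 1 = -11.1%.
- k = 1: no change.
- k = 1/1.5 = 0.667: p = 0.10 gives 1/0.967 - 1 = +3.4%; p = 0.25 gives 1/0.917 - 1 = +9.1%.

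Both p and k are assumptions, and k sets the sign. These are crude rates, before the planned adjustment for age-band and comorbidities.

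**7. Sign that the populations were not separated.** Previous stroke is excluded in Case Ascertainment, yet Covariates adjusts for baseline stroke or TIA. Only the TIA part could still vary in a cohort free of previous stroke.

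**The case against.** The strongest reply is that the exclusions were meant only for the drug comparison. They suit that cohort, and a condensed article may leave the population for each analysis to a fuller document. This is plausible. But the article states the exclusions without limit, under a heading that covers all of Phase 1, so the ambiguity lies in the stated text.

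A reader might infer that the guideline aim cannot be answered at all. The documents do not support that. Statistical Analysis still counts untreated and antiplatelet-only cases, so the main prescribing question can be estimated in patients without previous stroke, with the distortion shown above. Nor do the exclusions remove off-guideline patients as a class: a previous stroke is not a departure from guidelines. The dose criterion comes from the British National Formulary while the stated standard is NICE, and the article does not say that one implies the other. Whether off-formulary dosing counts as a guideline departure is therefore open; that it cannot be measured after the exclusion is not.

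A reader might also infer that a cleaned DOAC group meets an unfiltered warfarin group, biased in favour of DOAC. Two of the three exclusions apply to warfarin users as well, and the direction depends on an unknown rate ratio. Recommended-dose DOAC versus warfarin is a legitimate question, and the Discussion's reference to a population effect is a loose phrase rather than a defined estimand. It shows some tension with the dose restriction, not a contradiction.

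**Conclusion.** The point holds in a limited form. The conflict between the two primary statements is explicit and rests on no assumption. Followed as written, the Phase 1 exclusions have three effects: DOAC-dose concordance is 100% by construction and cannot be estimated; management of AF patients with previous stroke cannot be described; and the yearly incidence, prevalence and treatment figures describe a selected population. The treated share is biased downward for the population without previous stroke. That direction follows from the algebra if the dose exclusion governs the descriptive analyses, but the size needs inputs the article does not give. The remainder of the guideline aim is restricted, not lost. For the drug comparison, the one-sided dose filter is a reason for a sensitivity analysis, with no size or direction of bias established.

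**What to change.** (a) State one primary objective, identically in the Abstract and the Introduction, and place the other question below it. Extraction ended in May 2019 and analysis in December 2019, so if the choice is being made after analysis, say so.

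(b) Define two populations. Use all adults with coded AF for the incidence, prevalence, treatment and guideline analyses. Limit the previous-stroke, DOAC-dose and 90-day-gap exclusions to the DOAC-versus-warfarin cohort. Reconcile this with the baseline stroke or TIA covariate, for example by stating that only TIA is adjusted for in that cohort.

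(c) Add a sensitivity analysis of the drug comparison without the DOAC-dose restriction. Making all DOAC initiators the main analysis would be a different estimand and is not required.

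Cost: rewording, re-run descriptive tables, one extra sensitivity table and a disclosure that the clarification is post hoc. If the exclusions were applied at extraction, which the article does not say, the descriptive tables would also need a new extract.

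### The inclusion rule dates registration rather than diagnosis, so the DOAC-versus-warfarin comparison in newly diagnosed AF admits AF diagnosed years before the study window

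*Protocol article*

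**What the plan says.** The end of the Introduction in the Protocol article sets the primary objective: whether "people with newly diagnosed AF treated with DOACs versus warfarin have any difference in stroke or all-cause mortality in long-term follow-up".

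Eligibility is given once, under Methods, Case Ascertainment. It takes in adults with a "code for the diagnosis of AF who had been registered at any point between 2008 and 2019". The exclusions in the same paragraph are: "We excluded patients who had a previous stroke and those not on British National Formulary–recommended dose of DOAC".

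Two other places describe the cases differently. The abstract (Methods) says "AF cases from 2009 to 2019 were identified". Study Design says "We conducted a repeated cross-sectional study to identify those patients diagnosed with AF during 2009-2019". Data Source repeats the design label: "The initial phase involved a repeated cross-sectional retrospective analysis of data extracted from the RCGP RSC database".

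Exposures and Outcomes defines treatment entry: "We considered the exposure as continuous anticoagulant prescription for the first time after receiving an AF diagnosis". It adds that, where treatment began in hospital, exposure is still counted from the first general practice prescription, and that patients are followed to the end of the study period. Statistical Analysis then plans cause-specific and subdistribution hazard ratios. Separately, it plans yearly incidence, prevalence and treatment shares in incident and prevalent cases.

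**The concern.** The objective, the inclusion rule and the design label describe different studies. The objective needs people whose AF began within the period studied, followed from the start of treatment. The rule needs only an AF code of any date in someone registered at some time in 2008-2019.

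Two things are at stake. First, if patients with long-standing AF enter the comparison, the hazard ratios describe a mixture of disease durations and do not answer the stated question. Such patients have also, by construction, reached their first prescription alive and without a stroke. Second, two teams applying the document could build different cohorts, one by registration from 2008 and one by diagnosis from 2009, and both could claim to have followed it.

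**Working it through.** The plan gives no sample size, event count or share of prevalent cases for this comparison, so there is no figure to reproduce. The check sets the sections against each other.

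**Which date is constrained?** In Case Ascertainment the 2008-2019 limits apply to registration. Nothing in the rule limits the date of the AF code. In Study Design the 2009-2019 limits apply to diagnosis. The two differ in criterion and, by 2009 − 2008 = 1 year, in start.

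**Who gets in?** Illustrative patients, all adults with no earlier stroke:

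| Patient | Case Ascertainment | Study Design | Objective |
|---|---|---|---|
| A: AF coded 2001, still registered in 2008, first general practice anticoagulant prescription 2014 | In | Out | Not newly diagnosed |
| B: AF first coded in 2008 while registered | In | Out | Depends on a window the text does not settle |
| C: AF first coded within 2009-2019 while registered | In | In | Newly diagnosed |

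Patient A starts treatment 2014 − 2001 = 13 years after diagnosis and breaks no rule in Case Ascertainment or Exposures and Outcomes.

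**Do the exclusions remove patient A?** No. Previous stroke, the DOAC dose condition and a gap of more than 90 days between prescriptions do not depend on when AF was diagnosed.

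**Does the exposure rule remove patient A?** No. It asks for a first prescription after diagnosis and sets no limit on the time between the two. It secures a new start of treatment, not a new diagnosis.

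**Does it secure a new start for everyone?** Not fully as written. Exposure runs from the first general practice prescription, so a hospital starter is indexed after treatment has begun. For a patient who transfers in already treated, the result depends on whether earlier prescriptions can be seen, and the text states no look-back. Some such patients could be indexed as new starters.

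**Does adjustment deal with it?** The listed covariates are age-band, gender, deprivation quintile, comorbidities from the stroke risk score and smoking. Time since diagnosis is not among them.

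**Does the design label fit?** A repeated cross-section fits the yearly incidence, prevalence and treatment shares. The hazard analysis starts at a first prescription and follows people to study end, which is a retrospective cohort.

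**The case against.** The strongest reply is that the document signals the intended population elsewhere. The objective says newly diagnosed, Study Design says diagnosed in 2009-2019, and a broad pool is needed anyway for annual prevalence. On that view Case Ascertainment simply fails to say which analysis it serves. This is a plausible account of what was meant, but it does not settle the matter. Case Ascertainment is the only inclusion rule, it is not tied to the descriptive part, and its dates disagree with Study Design.

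A second reply is that Exposures and Outcomes already describes new treatment and follow-up. That stands in part. Follow-up and a time origin are present, so it would be wrong to infer that the cross-sectional label prevents hazard ratios from being estimated. The label is only incomplete. A reader might also infer that long-established warfarin users enter wholesale as new starters and that this favours warfarin. The document does not support that. Entry of treated patients is possible only where earlier prescriptions are not visible, nothing says that prescribing history is cut off, and a patient such as A could start either drug.

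A third reply is that an article may leave look-back and prior registration to a fuller document. That is accepted: their absence is not the fault here. The fault is that the stated rule, the stated objective and the stated dates disagree.

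**Conclusion.** The point holds as an inconsistency in what the document states. The inclusion rule admits AF diagnosed long before the window to a comparison meant for newly diagnosed AF. The criterion and start year conflict with those in the abstract and Study Design. The design label does not describe the comparative analysis. This should be corrected, because it changes who is in the analysis of the primary objective.

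No size can be put on it. A reader might try to estimate the prevalent share from assumed AF prevalence and incidence. Those rates are not in the document, and the result would describe everyone with an AF code, including untreated and antiplatelet-only patients, not the treated cohort left after the first-prescription rule and the gap exclusion. The direction of any bias is likewise not derivable. Confidence is high for the inconsistency. The possible entry of already-treated patients is conditional on what the records show.

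**What to change.** For the DOAC-versus-warfarin comparison, define a retrospective cohort explicitly:

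- first-ever AF code within one stated window, with 2008 and 2009 reconciled and the same dates used in the abstract, Study Design and Case Ascertainment;
- a stated period of registration before that code, so that the code can be taken as new and earlier prescriptions can be seen;
- no anticoagulant prescription before the index prescription, with follow-up starting at the index prescription.

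Keep the present broad rule and the repeated cross-sectional design for the annual incidence, prevalence and treatment shares, and say that they serve that purpose only.

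The cost is more than wording. Extraction was completed in May 2019 and phase 1 analysis in December 2019, so the comparison would have to be re-run if the cohort was built on the registration rule. No new extraction should be needed, provided that diagnosis dates, registration dates and prescribing history are in the extracted data. The cohort will be smaller, which is a tolerable loss in a database of more than 3.5 million patients. If the cohort was in fact restricted to AF first diagnosed within 2009-2019, with prior registration and no earlier anticoagulant prescription, correcting the text is enough.
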